##### Development of the manuals: coproduction with experts by experience

The 6 modules/manuals of Better Living with Non-memory-led Dementia have been co-produced with a group of experts by experience (EbE) (people with dementia and/or their relatives) through an iterative process with investigator [name]. Members of the organisation Rare Dementia Support were invited to join the co-production group. Distribution of a call for experts by experience flyers was used for this purpose (these flyers were co-produced with a couple of EbE and can be found in Supplementary material). Twenty-one EbE joined the co-production group between end of 2019 and 2021. Due to the Covid-19 pandemic, most meetings took place over videoconference and, exceptionally, phone or face to face (17 videoconferences, 1 phone call and 1 face-to-face meeting). There was also extensive correspondence by email between the EbE group and [name]. The subgroup of EbE working on the manuals for bvFTD was entirely composed by relatives of people with bvFTD, and meetings took place as a group. This was due to the difficulty to engage people with bvFTD in the process given the behavioural features and lack of insight characterising the condition. In the groups working on the PCA and PPA manuals, there was representation of people living with the condition. To support the participation of the person with dementia, these meetings took place one to one between [name] and the person living with dementia and their relatives. Briefly, the procedure for the meetings involved (1) sending supporting material before the meeting and information about how to prepare (created following easy-to-read and inclusive guidelines); (2) asking about preferred forms of communication prior to the meeting; (3) sending questions in advance to be asked during the meeting, so the person with dementia could have time to think and write down their responses if needed; and (4) sending minutes after the meetings in an accessible format for the person with dementia and their relatives to review together. This last step proved an important opportunity to correct inaccuracies and misunderstandings.

In the early stages of the development of the manuals, the work with the EbE group focused on the structure of the manuals and main messages to come across. For instance, one of our EbE with PPA wrote, ‘I would like people to understand that this is the way I speak, I have a condition, people need to be more patient’. The husband of a person with PCA said about the manuals, ‘they should be written in a positive way and convey hope’. The EbE group provided extensive advice about what symptoms to address in the programme and how, top priorities in management of symptoms, what strategies were more important to consider, they shared real situations to be include as vignettes, made suggestions about options for respite and support, identified common barriers to implement symptom management strategies and shared tips of how they had overcome them, how they managed difficult emotions (e.g. shame, guilt), deal with legal issues, relationships with others, and how they introduced companions and advice on what vocabulary to use in the manuals. The group preferred that all the material and resources from the course were also provided in a printable format (not only on the web) so people could share it with relatives and friends. The group also advised on the development of the website to host the education programme. Wireframes of the website were shared with the group either in videoconference meeting or by email, and their feedback was incorporated. In the late stages of the development process, drafts of the manuals were circulated by email for EbE to review. It was predominantly EbE who were relatives, and not people with dementia, which contributed to this last round. They sent feedback as notes in emails or direct corrections in the drafts of the manuals (either typed or handwritten). The group would also share personal resources they had found useful to understand their relative’s condition, to manage symptoms and their own well-being. Some members of the EbE group also contributed to the final proofreading.

The work of co-production took place between October 2019 and March 2022. The final draft of the manuals also received input from educational group facilitators and went through several rounds of proofreading with academic and clinical colleagues.

##### Content of the manuals

Six learning modules per phenotype (PCA, PPA, bvFTD) resulted from the co-production phase, making 18 in total. The first 3 modules are phenotype specific. The fourth one is common across phenotypes since it is focussed on caregiver wellbeing. The fifth module in each set contains a list of resources relevant across phenotypes (e.g. charities and organisations that can provide support), and the sixth one is an introduction to phenotype-specific support groups with links to three support group webinars each. Together, the 18 manuals contain 49 purpose-build illustrations, 53 vignettes and 44 links to external resources (e.g. videorecording of support meetings).

##### Accessibility

In Brotherhood et al., [31], we referred to enhancing the accessibility of the intervention for those with disability. However, during co-production, it became apparent that such measures were not necessary. The PPI group noted that there are already many freely available accessibility tools widely used by the community of people with reading and visual disabilities.

### Comparison

The control group (wait-list) will receive treatment as usual, consisting of explicit signposting to the publicly available Rare Dementia Support website and will continue with any kind of support the participants may already being receiving (e.g. psychological support, online information, support groups). They will be given access to the intervention at the end of the study.

### Procedures

The flow of events for participants in this study is as follows:Participants give online consent to take part in the study.Once consent is given, they receive a link to a Qualtrics survey to complete online demographic information and baseline outcome measures.After the surveys are filled out, participants are randomised and notified of whether they will be given access to the intervention or to treatment as usual.Participants in the intervention group receive an email with a link (unique for each participant) to access the online intervention. Clicking on this link will give them access to a bespoken online platform purposely built for this study. Participants are encouraged to go through the 6 modules comprising the programme (the 6 modules are available at the same time). They are also encouraged to engage with the programme facilitator via email, to reflect on their experience putting in practice the skills learnt in modules 2, 3 and 4. The intervention is tailored to each phenotype: participants caring for a person with PCA only access the PCA modules, etc.Participants in the control group are redirected to an existing website about rare dementia. They do not receive additional support.Eight weeks after randomisation and access to the programme (or redirection to the website) has been granted, participants receive a new link to Qualtrics to complete follow-up outcome measures. This is repeated 3 months after randomisation.

### Data collection, management and analysis

#### Demographics

After giving consent, participants will fill in an online survey with demographic information before start completing the baseline measures.

#### Feasibility measures

The following feasibility measures will be collected:Recruitment processNumber of people agreeing to be sent information about the study.Proportion of participants who agree to participate.Proportion of eligible participants who agree to participate.Potential inequalities in recruitment feasibility will be assessed by comparing basic data on ethnicity age, gender and diagnosis of care recipient between Rare Dementia Support members, those who are screened as eligible for and those who consent to the study.RetentionThe analysis will consider the points from the CONSORT checklist for randomised pilot and feasibility trials [57] to ensure that all topics are being covered. Values for eligibility rates, recruitment rates, attrition rates and withdrawal rates will be reported using the participant flow data collected within the study. This will be evaluated overall and per group.Furthermore, details on reasons for ineligibility and non-recruitment will be reported within a table along with their related patient frequencies and percentages. Information on withdrawals and nonrespondents will be presented including reasons where applicable and time points during the trial.Feasibility of measurement toolsTime taken to fill in questionnaires (with consideration for outlier times to be those where participants have left the questionnaire to complete at another time).Missing data from questionnaires (questionnaires will be implemented using the Qualtrics function that reminds participants when they have not filled in an item, but will not force a choice).Follow-up response rates (8-week and 3-month post-randomisation).

#### Acceptability measures

We used the definition of acceptability recently proposed by [58] to decide on the following acceptability measures:

##### a) Prospective acceptability 

Burden (reasons for not taking part or discontinuation).Percentage who completed baseline measures agreeing to be randomised and reasons for not taking part in randomisation.Answers to qualitative questions in baseline questionnaire about how they feel about the intervention (e.g. how do you feel about taking part in this course?), burden (e.g. how much effort do you think will be involved in taking part in this study?) and ethicality (e.g. do you have any ethical concerns about taking part in the course? If yes, what would these be? (See Appendix  III).

##### b) Concurrent acceptability

Intervention coherence and adherenceoTask completion rate after every module.oNumber of interactions with facilitator.

##### c) Retrospective acceptability 

It will be measured in two ways:To capture views of everyone participating in the study, follow-up measures will include a brief acceptability questionnaire designed to assess opportunity costs and perceived effectiveness. The health economic questions used for the control and intervention group will differ: participants in the intervention arm will be asked questions on resource use and questions on willingness to pay, whilst those in the wait-list control arm will be asked about resource-use only. Participants in the wait-list control arm will be asked about acceptability of filling in the measures at each time point. Participants in the intervention group will be asked about acceptability of the intervention (see Appendix III).A more in-depth qualitative interview focussed on the above headers (as well as mechanisms of change) will be given to a smaller number (n~15) of purposively sampled individuals.

#### Proposed clinical measures

The range of clinical outcomes encompassing self-efficacy, relationship with care recipient, psychological status, quality of life and health and social health will be assessed at baseline line, 8-week and 3-month post-randomisation. An additional section about health economics will be added to explore the feasibility of evaluating the costs of the educational programme in a larger trial. We will be using the following measures:WHO 5 Well-being Index [59]GAD-7 [60]PHQ-9 [61]De Jong Gierveld Loneliness Scale [62]Lubben Social Network Scale [63]Pearlin Mastery Scale [64]Caregiver Self-Efficacy Scale [65]Dementia Management Strategies Scale [66]The quality of carer-partner relationship scale [67]Health economics questions (developed by the health economic collaborators, [name] and BA) (see Appendix  III).

The recommended SPIRIT schedule for the enrolment or participants, administration of the intervention and assessment time points is shown in Table 1.

**Table 1 Tab1:**
[figure not shown]
SPIRIT participant timeline with time schedule of enrolment, intervention implementation, and assessment time points

^*^Recommended content can be displayed using various schematic formats. See SPIRIT 2013 explanation and elaboration for examples from protocols

^**^List specific time points in this row

### Statistical analysis

#### Quantitative data

All analysis will be guided by the principle of intention to treat. There will be a preliminary analysis of intervention outcomes. Point estimates and 95% confidence intervals will be calculated using adjusted means from the analysis and used to estimate standard deviations and effect sizes for continuous data. Means and standard deviations of response rates for count data and proportions in each category will be provided. These will be used to confirm the sample size calculation for a definitive study. Dependent on the recruitment within each diagnosis group, we may consider presenting preliminary results within diagnosis groups. Exploratory analysis will be performed to determine the most appropriate model of analysis for a definitive RCT, including consideration of the further possible covariates and factors to be included in an analysis model. All quantitative analysis will be completed using Stata 17, SPSS v25 and R version 3.

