**Methods:**

A randomised controlled feasibility trial will be conducted on a sample of 30 caregivers of people living with PCA, PPA and bvFTD. Participants will be recruited among members of the support organisation Rare Dementia Support (based at UCL in the UK). The intervention group will be given access to an 8-week co-produced web-based educational programme consisting of 6 modules addressing education about PCA, PPA and bvFTD and support strategies for the person with dementia and for the caregiver. The control group will receive treatment as usual (TAU). Feasibility will be measured through feasibility of recruitment, clinical measurement tools and acceptability. Clinical measures will be used to assess preliminary efficacy and data on completion rates, missing data and variability used to decide on measures to be included in a full-scale trial.

Allocation ratio will be 2:1 (intervention:control) stratified by diagnosis. Feasibility of recruitment and acceptability will be assessed. Clinical measures will be administered at baseline and 8-week and 3-month post-randomisation. The control group will be offered access to the intervention at the completion of data collection. Participants will be unblinded, and all measures will be self-reported online.

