## Aims and objectives

The aim of this study is to test the feasibility of the Better Living with Non-memory-led Dementia programme. The objectives are as follows:Primary: To assess feasibility of recruitment, feasibility of measurement tools and acceptability (prospective, concurrent and retrospective).Secondary: To assess the preliminary efficacy, understood as directionality on the clinical measures (that can inform optimal outcomes measure in a full trial).

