### Power calculation

As this is a feasibility study, a formal power calculation is not required; however, the sample size does require justification. This study was initially intended to develop a tool for carers of people with bvFTD only. However, during the interviews with stakeholders, became apparent the need and opportunity to develop two more tools, to cover PPA and PCA (details of sample calculation for bvFTD only can be found in Brotherhood et al., [31]. Originally, we aimed to recruit 135 participants comprising 45 caregivers from each of the three diagnostic groups that the intervention is designed for (PCA, PPA, bvFTD) with a 30:15 intervention control split in a 2:1 randomisation. This would have provided both a precise estimation of the overall retention rate but also within diagnostic group. Reviewing this target once recruitment was underway, we acknowledged that this would be a large feasibility study, and with a rarer disease, it would require recruiting a large proportion of the available population. Therefore, we revised the target sample down to 30 participants (randomised 20:10 in favour of the intervention); this would allow an understanding of the trial processes, allow for adaptation and refinement of the intervention and understand acceptability and fidelity within the population. The confidence intervals on our estimates will be wider, but this is an acceptable concession given the sparsity of the potential population to recruit. We will achieve a 95% confidence interval of ±18.7% around our expected value of 76% of those completing the intervention and pre-post measures whilst viewing 70+% sessions. In terms of retention to the study, we will achieve a 95% confidence interval of ±15.5% around our expected value of 75%.

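### Direction of effect and pilot effect sizes from a 20:10 sample are too imprecise to inform the full trial's choice of outcome or to help confirm its sample size

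*Protocol article*

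**What the plan says.** Three places in the protocol article bear on how the pilot results feed the full trial.

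- **Aims and objectives.** The secondary objective is preliminary efficacy, "understood as directionality on the clinical measures (that can inform optimal outcomes measure in a full trial").
- **Abstract, Methods.** Clinical measures serve to assess preliminary efficacy, with "data on completion rates, missing data and variability used to decide on measures to be included in a full-scale trial".
- **Statistical analysis, Quantitative data.** The estimates and their 95% limits "will be calculated using adjusted means from the analysis and used to estimate standard deviations and effect sizes for continuous data". After a sentence on count data and proportions, the text continues: "These will be used to confirm the sample size calculation for a definitive study".

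On sample size, the Power calculation section states: "As this is a feasibility study, a formal power calculation is not required; however, the sample size does require justification". It then reports that "we revised the target sample down to 30 participants (randomised 20:10 in favour of the intervention"), and justifies that number by the precision of two proportions: "We will achieve a 95% confidence interval of ±18.7% around our expected value of 76"% for completion, and "we will achieve a 95% confidence interval of ±15.5% around our expected value of 75"% for retention. It gives no precision for any between-arm effect.

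**The concern.** There are two linked difficulties.

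First, the objectives and the Abstract give different bases for carrying a measure forward. The Abstract's criteria are properties of the measure that a pilot can observe. The direction of a between-arm difference is a treatment-effect estimate, and in a sample this small its sign is often decided by chance. A good measure could count as less suitable because its estimate happened to fall on the wrong side of zero.

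Second, the analysis section places effect sizes among the quantities used to confirm the definitive sample size. If a large estimate arises by chance, it can appear to endorse a trial that is too small. If a small one arises by chance, it can cast doubt on an adequate trial. The Discussion in the Abstract says that this pilot will inform a fully powered international trial, so an error would pass straight into that trial.

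**Working it through.** **1. The plan's own figures.** The Wald half-width is 1.96 × √(p(1−p)/n).

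- Completion, p = 0.76, n = 20 (intervention arm): 1.96 × √(0.76 × 0.24/20) = 18.7%.
- Retention, p = 0.75, n = 30 (whole sample): 1.96 × √(0.75 × 0.25/30) = 15.5%.

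Both reproduce. They concern proportions and say nothing about effect sizes.

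**2. Inputs for the effect size.** From the protocol: 20 and 10 randomised, and 75% expected retention, which is about 15 and 7.5 with follow-up. Assumed, because the protocol gives no values: a true standardised effect d of 0.2, 0.3 or 0.5, and a baseline-to-follow-up correlation r of 0 (no gain from adjustment) or 0.6.

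**3. Precision of a standardised difference.** SE = √(1/n₁ + 1/n₂) × √(1 − r²), and the half-width is 1.96 × SE. At r = 0.6 the second factor is √(1 − 0.36) = 0.8.

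**4. Probability that one scale shows the wrong sign.** This is Φ(−d/SE). For example, at 20:10, r = 0 and d = 0.3, Φ(−0.3/0.387) = 0.22.

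| Arms with data | r | SE | 95% half-width (SD) | Wrong sign, d = 0.2 | d = 0.3 | d = 0.5 |
|---|---|---|---|---|---|---|
| 20:10 | 0 | 0.387 | ±0.76 | 30% | 22% | 10% |
| 20:10 | 0.6 | 0.310 | ±0.61 | 26% | 17% | 5% |
| 15:7.5 | 0 | 0.447 | ±0.88 | 33% | 25% | 13% |
| 15:7.5 | 0.6 | 0.358 | ±0.70 | 29% | 20% | 8% |

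These use the normal approximation. With t quantiles, the unadjusted 20:10 half-width is slightly wider, at ±0.79. The protocol lists nine scales besides the health economics questions. At 20:10, r = 0 and d = 0.3 on every scale, about 9 × 0.22 = 2 would be expected to point the wrong way.

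**5. What the pilot can supply, and how well.** A standard deviation is a legitimate pilot estimate, but its uncertainty matters. At 28 degrees of freedom the 95% interval for the true SD runs from 0.79 to 1.35 times the estimate. The required sample size varies with the SD squared, so it ranges from 0.63 to 1.83 times the planned figure.

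**6. Which SD.** An SD from an adjusted analysis is a residual SD. If the adjustment includes baseline, it is about √(1 − r²) times the raw SD: 0.87 at r = 0.5 and 0.71 at r = 0.7. In a formula for an unadjusted comparison it would understate the sample size by r², that is 25% and 49%. In a formula for an adjusted analysis it is the right input, provided the correlation is not applied again.

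**The case against.** The strongest reply is that the protocol commits to less than this. The objective only permits direction to inform the choice. The Abstract names other criteria, the Progression criteria section assesses the suitability of outcome measures qualitatively, and questionnaire time, missing data and acceptability are already collected. The analysis section speaks of confirming a sample-size calculation, which implies that one exists on another basis, and SDs and response rates are proper pilot inputs. The analysis is called preliminary, and the Randomisation section says no inferential statistics will be generated. The primary objectives and the quantitative progression criteria do not use effect estimates.

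Most of this stands, and it limits the point in four ways.

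- A reader might infer that effect direction will select the outcomes and that noise will set the sample size. The documents do not support that: direction is one permitted input, and the effect size is part of a check.
- A reader might infer that the scale with the largest observed effect will be chosen and the full trial powered on it. No such rule is stated, so figures built on that scenario do not measure this plan's fault.
- A residual SD is not an error in itself. The section names neither the covariates nor the formula in which the SD would be used.
- To say that direction cannot be estimated at all would be too strong. At d = 0.5 the sign would be right in 87 to 95% of pilots.

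Two things remain. The objectives and the Abstract still give different bases for choosing measures, and effect sizes are still among the results used to confirm the definitive sample size. The article gives no precision for that use, and the calculation shows that it is poor.

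**Conclusion.** The point holds in a limited form and is a should-fix. The plan lets direction of effect inform outcome choice, at odds with the criteria in its Abstract, and lets pilot effect sizes help confirm the definitive sample size. A sample of 20:10 supports neither use. The 95% interval for a standardised difference extends ±0.76 SD (±0.88 at 75% retention), and still ±0.61 to ±0.70 with a baseline correlation of 0.6. Such an interval does not separate no effect from effects well above those assumed here. Across both retention levels and both correlations, the wrong-sign probability for one scale is 26 to 33% at d = 0.2, 17 to 25% at d = 0.3 and 5 to 13% at d = 0.5. The unadjusted half-width at 20:10 rests on the planned numbers alone, and the one at 75% retention adds the plan's expected retention. The adjusted half-widths and all wrong-sign probabilities rest on assumed values of r and d. The feasibility objectives and progression criteria are unaffected.

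**What to change.** - **Aims and objectives:** remove direction of effect as a basis for choosing outcomes. Align the sentence with the Abstract (completion, missing data, variability), and add the acceptability and completion-time data already being collected.
- **Quantitative data, reporting:** state that between-arm estimates with 95% confidence intervals are descriptive only.
- **Quantitative data, sample size:** state that the definitive sample size will rest on a prespecified important difference. The pilot will supply the SD with its uncertainty (for example its 95% interval), the baseline-to-follow-up correlation, retention and missingness, but not the observed effect size. The value of that difference can be left to the definitive trial's protocol.
- **Quantitative data, SD:** say whether the SD is raw or residual. Use a residual SD only in a formula for an adjusted analysis, and do not apply the baseline correlation a second time.

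The cost is wording in two sections, with no extra data or participants. The downside is that the definitive sample size may become larger, which matters in a population that the protocol describes as sparse.
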